### Statistical Analyses

We will analyze all data according to a prespecified statistical analysis plan developed and finalized before any investigator is unblinded.

Following the intention-to-treat principle, we will analyze patients in the treatment groups to which they were randomized. For both coprimary outcomes, we will compare all patients allocated to the PVC-RAM-3 intervention to all patients allocated to standard care.

For coprimary 1 (composite of hospital readmission or emergency department visit), we will compute the time to event from the discharge date and plot the cumulative incidence curves between the two treatment groups. We will use a Cox regression model to obtain hazard ratios and 95% CIs. Any acute hospital care event that occurs before patients undergo their index surgery, in cases where surgery is postponed, will not be included in this outcome.

For coprimary 2 (index hospital LOS), we will calculate the hospital LOS for both groups and compare them with a 2-sample Wilcoxon rank sum test. Given the large sample size, the 2-sample Wilcoxon rank sum test will produce results that will be similar to the 2-sample *t* test.

For the coprimary outcome analyses, we will censor patients whose surgeries were canceled and not rescheduled within 30 days of randomization.

VC-RAM will be considered effective if either of the 2 coprimary efficacy analyses is significant. We will use a gatekeeping with a fallback procedure to analyze their statistical significance [12]. We will start with an overall α of .05, split between the two outcomes with a computed 2-sided *P* value less than an α of .04 for postdischarge acute hospital care and less than an α of .01 for index length of hospital stay. If the first coprimary outcome achieves significance at an α level of <.04, the α from this test will be added to the second coprimary outcome’s α (ie, the α will be .05). However, if the first coprimary outcome is not significant, the second coprimary outcome will be tested at an α level of <.01.

For secondary and tertiary outcomes, we will use the chi-square test for binary or categorical variables and the 2-sample *t* test for continuous variables. We will assess the effect of VC-RAM using log-binomial regression models and report the corresponding relative risks and 95% CIs. For continuous outcomes, we will evaluate the intervention effect using analysis of covariance regression models to obtain effect estimates and their 95% CIs. Depending on the frequency of time-to-event outcomes, we may use the log-rank test to assess differences between groups. The α level for all secondary and tertiary outcomes will be set at .05. For the secondary and tertiary outcomes, we will not adjust for multiple testing as we will be evaluating the consistency of effect, number of outcomes, and size of the effect to offer insights into the reliability of any statistically positive secondary or tertiary outcomes. Economic analysis (Multimedia Appendix 7) will be done in a separate protocol and publication.

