**Objective:**

The Post Discharge After Surgery Virtual Care with Remote Automated Monitoring Technology-3 (PCV-RAM-3) trial tests the hypothesis that informing surgeons and patients of virtual care with remote automated monitoring (VC-RAM) assignment will promote earlier discharge, thereby reducing the index length of hospital stay, and that postdischarge VC-RAM will reduce acute hospital care.

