### Trial Outcomes

The PVC-RAM-1 trial provided encouraging data that virtual care with RAM may reduce acute hospital care [8]. In PVC-RAM-3, we wanted to inform the impact on acute hospital care and the index length of hospital stay. Initial sample size calculation assumptions suggested index length of hospital stay would require a larger sample size than acute hospital care. To avoid being underpowered by these outcomes, we made the index length of hospital stay the primary outcome. At the time of the final interim analysis, blinded overall data on the LOS and acute hospital care indicated there was adequate power to split the α and evaluate two coprimary outcomes (ie, acute hospital care and length of hospital stay). Consequently, we revised the primary outcome to include both index LOS and postdischarge acute hospital care as coprimary outcomes, making this change without any knowledge of the trial results.

The primary objective of this trial is to determine whether VC-RAM, compared with standard care after elective surgery, and informing surgeons and patients of VC-RAM allocation, reduces the occurrence of the coprimary outcomes within 30 days of randomization. The first coprimary outcome is postdischarge acute hospital care (defined as hospital readmission or emergency department visit) within 30 days after randomization. The second coprimary outcome is index hospital LOS (ie, time from the end of surgery to index hospital discharge).

Secondary outcomes during the first 30 days after randomization include (1) hospital readmission; (2) emergency department visit; (3) medication error detection; (4) medication error correction; (5) surgical site infection; (6) days in hospital; (7) pain of any severity, and moderate to severe pain assessed at 15 and 30 days after randomization; (8) proportion of patients with the atherosclerotic disease taking classes of efficacious medications at 30 days, (ie, an antiplatelet or anticoagulant drug, an angiotensin-converting enzyme inhibitor or angiotensin-receptor blocker, and a statin); and (9) the proportion of active smokers before surgery receiving pharmacological smoking cessation interventions at 30 days after randomization. Outcome definitions are presented in Multimedia Appendix 5.

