### Follow-Up

The day of randomization is day 1 of the trial, and all patients undergo 30 days of follow-up. Study personnel contact patients on day 30 to collect data on acute hospital care, secondary and tertiary outcomes, medication error detection and corrections, and current medications. The EQ-5D-5L is administered at baseline and day 30, and the Brief Pain Inventory-Short Form is administered on days 15 and 30. In the virtual care group, virtual nurses collect data on medication error detection and corrections throughout the intervention period.

If a patient reports an event, study personnel obtain source documentation from hospital or family physician records. If patients cannot be contacted directly, study personnel reach out to a designated relative, friend, or primary care physician. Study personnel and virtual nurses record all data in case report forms that are then entered into an electronic data capture system (Trial Master).

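### The acute-care coprimary is defined over 30 days from randomisation but timed from discharge, a date the intervention is meant to move; the effect is small, and a 30-day risk comparison from randomisation would remove the mismatch

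*Protocol article*

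**What the plan says.** All references are to the protocol article.

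- **Outcome.** Trial Outcomes defines coprimary 1 as "postdischarge acute hospital care (defined as hospital readmission or emergency department visit) within 30 days after randomization".
- **Follow-up.** The Follow-Up section anchors everything to randomisation: "The day of randomization is day 1 of the trial, and all patients undergo 30 days of follow-up".
- **Analysis.** Under Statistical Analyses, for coprimary 1, "we will compute the time to event from the discharge date and plot the cumulative incidence curves between the two treatment groups". The next sentence reads: "We will use a Cox regression model to obtain hazard ratios and 95% CIs".
- **Discharge as a treatment effect.** The abstract's Objective states that knowledge of VC-RAM assignment "will promote earlier discharge, thereby reducing the index length of hospital stay". Trial Outcomes makes the interval from end of surgery to index discharge the second coprimary.
- **Population.** Statistical Analyses promises an intention-to-treat comparison of everyone allocated. It adds that patients whose surgery is cancelled and not rescheduled within 30 days of randomisation are censored.

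The article does not reconcile the two time origins. It also states no comparison of the composite by day 30 from randomisation.

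**The concern.** Discharge would be a natural time zero if patients were randomised at discharge. Here they are randomised before surgery, and surgeon and patient are told the allocation so that discharge can come earlier. Three things follow.

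1. At equal time since discharge, a VC-RAM patient sent home early is compared with a control at a later postoperative day.
2. The window closes at day 30 from randomisation, so earlier discharge lengthens the time in which an event can count. A model on the discharge clock does not register events that arise only from those extra days. The Discussion itself raises the possibility that shorter stays lead to more acute care.
3. Patients who die in hospital, are still inpatients at day 30 or have surgery cancelled have no index discharge. On this clock they contribute nothing, and censoring the cancelled patients has no effect.

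This coprimary is tested at α = .04, can by itself lead to VC-RAM being called effective, and passes its α to the length-of-stay test if significant.

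**Working it through.** **Step 1: the stated power.** Inputs from Sample Size Calculations: 1250 per group, 14% v 9.8%, two-sided α = .04, log-rank test, stated power 88.7%.
- Expected events: 1250 × (0.14 + 0.098) = 297.5.
- Implied hazard ratio: ln(1 − 0.098) / ln(1 − 0.14) = 0.684.
- Schoenfeld: Φ(√(297.5/4) × |ln 0.684| − 2.054) = 88.9%. Two proportions gives 88.3%.
- With a hazard ratio of 0.70 itself, Schoenfeld gives 84.7%.

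The stated figure reproduces, and it rests on cumulative risks of 14% and 9.8%.

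**Step 2: time at home.** Control mean stay is 2.5 days. If 35% of VC-RAM patients leave 1 day earlier, their mean is 2.5 − 0.35 = 2.15. Assume surgery on the day of randomisation. Time from discharge to day 30 is then 27.5 v 27.85 days, and 27.85/27.5 = 1.013.

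**Step 3: same hazard after discharge in both arms.** Assume all controls leave at day 2.5 and the hazard is constant.
- Daily hazard: −ln(0.86)/27.5 = 0.00548.
- Risk for a patient leaving 1 day earlier: 1 − exp(−0.00548 × 28.5) = 14.47%.
- VC-RAM risk: 0.65 × 14% + 0.35 × 14.47% = 14.16%.
- 30-day risk ratio: 14.16/14 = 1.012, while the discharge-clock hazard ratio is exactly 1.00.

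With a hazard that falls after discharge (Weibull shape 0.5), the risk ratio is 1.006. If every VC-RAM patient left 1 day earlier, it would be 1.017 to 1.034.

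**Step 4: hazard depends on time since surgery.** This was simulated with 2,000,000 patients per scenario. Assumptions: gamma stay with mean 2.5 days, Weibull hazard since surgery, control risk calibrated to 14%, no monitoring effect.

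| Weibull shape | Share leaving 1 day earlier | 30-day RR | HR, discharge clock | HR, randomisation clock |
|---|---|---|---|---|
| 1.0 | 35% | 1.0095 | 0.9985 | 1.0112 |
| 0.7 | 35% | 1.0237 | 1.0165 | 1.0270 |
| 0.5 | 35% | 1.0270 | 1.0225 | 1.0316 |
| 1.0 | 100% | 1.0375 | 1.0056 | 1.0432 |
| 0.7 | 100% | 1.0660 | 1.0458 | 1.0765 |
| 0.5 | 100% | 1.0835 | 1.0711 | 1.0979 |

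Simulation error on a single log RR is about √(2 × 0.86/140,000) = 0.0035. The contrast between clocks within a row uses the same simulated patients.

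Under the planned shift, RR divided by discharge-clock HR is 1.0095/0.9985 = 1.011, 1.0237/1.0165 = 1.007 and 1.0270/1.0225 = 1.004. If everyone leaves a day earlier, it runs from 1.0835/1.0711 = 1.012 to 1.0375/1.0056 = 1.032.

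**Step 5: against sampling error.** The standard error of the log hazard ratio is about 2/√297.5 = 0.116. ln(1.012) = 0.012, and 0.012/0.116 is about 0.1.

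**The case against.** The best defence is that the two statements can operate together: the 30-day window decides which events count, and discharge sets the time scale. The outcome is post-discharge, nobody can have the event while still in hospital, and monitoring starts the day after discharge. A time-to-event model also agrees with the log-rank basis of the power table. That is a fair reason to keep the discharge-clock model in the report. It does not make its hazard ratio the effect on the outcome as defined, because treatment moves the origin while the window stays tied to randomisation.

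Other parts of the defence stand and limit the point:

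- A reader might infer that the randomised comparison is lost. The figures do not support this. The distortion is about a tenth of a standard error under the planned shift, and where hazard falls with time since surgery most of the extra acute care still shows in the discharge-clock hazard ratio.
- A reader might infer that the bias could run either way. Every scenario examined went in one direction, towards understating harm from earlier discharge.
- Unequal follow-up after discharge does not by itself bias a Cox model if censoring is non-informative. The problem is the origin.
- The number of patients without a discharge date is unknown. A 5% share would be 0.05 × 2500 = 125, but 5% is only an assumption. With elective surgery, expected stays of 3 days or less and randomisation close to surgery, the group may be small.
- Readmission and emergency visits are each secondary outcomes within 30 days of randomisation, with log-binomial relative risks planned. What is missing is the same summary for their composite, the coprimary itself.

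Detail may sit in a statistical analysis plan that is not shown. The discharge origin is nevertheless stated in the article, so this is an inconsistency in what is written and not an omission.

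**Conclusion.** The point holds as an inconsistency between the defined outcome and its analysis, of modest size. If 35% of patients leave one day earlier, earlier discharge alone raises the 30-day risk ratio by about 1% to 3%, and the discharge clock misses about 0.4% to 1.2%. If every VC-RAM patient left a day earlier, it would miss about 1% to 3%. These figures assume surgery on the day of randomisation, a 14% control risk and the hazard shapes above. The documents do not support a claim of large bias or of a broken randomised comparison.

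Correction is still worthwhile. The understatement favours VC-RAM on the trade-off the Discussion raises, and patients without an index discharge fall outside a comparison meant to include everyone allocated. The power calculation, the visits prevented per 100 patients in the Discussion and the planned component analyses all use 30-day risk.

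**What to change.** Analyse the composite from randomisation to day 30 in all randomised patients and report the 30-day risk ratio and risk difference with confidence intervals. Treat death before the event as a competing event. Keep cancelled patients under the stated censoring rule, which takes effect once they have a time zero, and state the date at which they are censored. A Cox model with a randomisation origin is an alternative. The risk comparison reads more easily, because no one can have the event before discharge. Keep the discharge-origin Cox model as a supportive analysis.

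The article reports follow-up complete and analysis underway. If investigators are already unblinded, keep the prespecified model as it stands and report the randomisation-origin 30-day comparison beside it, labelled as added.

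The cost is a change to the analysis plan and program, using dates already collected. The stated power is unchanged, because it is built on cumulative risks of 14% and 9.8%. If 0.70 was meant as the effect before any earlier-discharge penalty, a 1% penalty gives 0.70 × 1.01 = 0.707, and two-proportion power falls from 88.3% to 86.7%. The main estimate loses its time-since-discharge reading, which the supportive model preserves.

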## Methods

### Design and Setting

The Post Discharge After Surgery Virtual Care with Remote Automated Monitoring Technology-3 (PVC-RAM-3) trial is a multicenter, parallel-group superiority randomized controlled trial involving 2500 patients undergoing elective noncardiac surgery at 3 Canadian hospitals: Hamilton General Hospital, Juravinski Hospital and Cancer Center, and St. Joseph’s Healthcare Hamilton. The trial evaluates the effects of VC-RAM compared to standard care post discharge. A study flow diagram is provided in Figure 1, and the SPIRIT (Standard Protocol Items: Recommendations for Interventional Trials) checklist is provided in Multimedia Appendix 1.

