### Randomization

Randomization occurs before surgery, after eligibility is confirmed, and informed consent is obtained. We randomize as close to the time of surgery as possible to minimize the risk of surgery postponement. Patients are randomized using an Interactive Web Randomization System, a 24-hour computerized system maintained by the coordinating center at the Population Health Research Institute, a joint institute of Hamilton Health Sciences and McMaster University in Hamilton, Ontario, Canada.

The randomization process uses block randomization with varying block sizes stratified by site, ensuring that study personnel and investigators remain unaware of block sizes. Patients are randomized in a 1:1 ratio to receive VC-RAM or standard care. Following randomization, research personnel notify the patient’s surgeon and the patient of the treatment allocation. Patients, health care providers, and data collectors are aware of treatment assignments, while outcome adjudicators remain blinded to treatment allocation.

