### Sample Size Calculations

Postdischarge acute hospital care and index hospital LOS are coprimary outcomes with a shared α. We allocate α=.04 for acute hospital care and α=.01 for index hospital LOS (details in Multimedia Appendix 6).

Table 1 presents the trial power for acute hospital care based on a log-rank test with a 2-sided α of .04 using SAS software (version 9.4; SAS Institute Inc). Assuming a 14% event rate in the control group, with an overall sample of size 2500 participants (1250 in the control group and 1250 in the treatment group), we will achieve 88.7% power to detect a relative risk reduction of at least 0.70 (30% relative risk reduction). Table 2 presents the trial power for index LOS based on a 2-sample Wilcoxon test assuming equal variance with a 2-sided α of .01. We expect patients in the standard care group to have a mean index hospital LOS of 2.5 days. If the knowledge that patients in the intervention group will receive virtual care with RAM after hospital discharge results in 35% of patients having their index hospital LOS reduced by 1 day, we will require a sample size of 2500 to have more than 80% power to detect this difference, with a 2-sided α of .01.

**Table 1 table1:** Power to detect an RR^a^ (0.65, or 0.70, or 0.75) based on log-rank test with a 2-sided α of .04 assuming control group event rates 12%, 14%, 16%, and 18% for a given total sample of size 2500, 2800, 3000, or 3200.

Sample size per group			RR 0.65 (35% reduction)							RR 0.70 (30% reduction)							RR 0.75 (25% reduction)				
			Assumed control event rate (%)		Treatment P (%)		Power (%)		Assumed control event rate (%)			Treatment P (%)		Power (%)		Assumed control event rate (%)			Treatment P (%)		Power (%)
**2500**			12		7.8		—^b^		12			8.4		—		12			9		—
	1250	—		—		93.3		—			—		82.5		—			—		65.5	
	1400	—		—		95.6		—			—		86.7		—			—		70.6	
	1500	—		—		96.7		—			—		89.0		—			—		73.7	
	1600	—		—		97.6		—			—		90.1		—			—		76.5	
**2800**			14		9.1		—		14			9.8		—		14			10.5		—
	1250	—		—		96.6		—			—		88.7		—			—		73.4	
	1400	—		—		98		—			—		92		—			—		78.3	
	1500	—		—		98.6		—			—		93.6		—			—		81.1	
	1600	—		—		99		—			—		95		—			—		83.6	
**3000**			16		10.4		—		16			11.2		—		16			12		—
	1250	—		—		98.4		—			—		93		—			—		80	
	1400	—		—		99.1		—			—		95.4		—			—		84.4	
	1500	—		—		99.4		—			—		96.5		—			—		86.8	
	1600	—		—		99.6		—			—		97.4		—			—		88.9	
**3200**			18		11.7		—		18			12.6		—		18			13.5		—
	1250	—		—		99.3		—			—		95.8		—			—		85.3	

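### The coprimary length-of-stay test ignores the site strata used in randomisation: valid but conservative, with a small loss of power if stay differs between hospitals

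*Protocol article*

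**What the plan says.** The Randomization section of the protocol article states: "The randomization process uses block randomization with varying block sizes stratified by site". Allocation is 1:1. The strata are three hospitals (Design and Setting).

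For the second coprimary outcome, index LOS, the Statistical Analyses section says the two groups' stays will be calculated and that the plan will "compare them with a 2-sample Wilcoxon rank sum test". It adds that, at this sample size, the result should be close to that of a two-sample t test. Table 2 bases the LOS power on the same unstratified test. Neither place mentions site.

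For the first coprimary outcome, acute hospital care, the article says only: "We will use a Cox regression model to obtain hazard ratios and 95% CIs". It neither names nor excludes strata or covariates. The same section refers to a separate plan: "We will analyze all data according to a prespecified statistical analysis plan developed and finalized before any investigator is unblinded". The alpha split is: "We allocate α=.04 for acute hospital care and α=.01 for index hospital LOS".

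**The concern.** When randomisation is blocked within site, the arms are balanced at every hospital, so between-hospital differences in LOS contribute almost nothing to the chance difference between arms. A pooled rank sum test does not know this. Its null variance includes the between-hospital spread, so its standard error is larger than the true one whenever hospitals differ. P values then tend to be too large, and power is lost.

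For LOS this is a stated choice and not a gap left for the analysis plan: the article names the coprimary test, and it is the unstratified one. Because LOS receives only α=.01 unless acute hospital care succeeds first, even a few points of power on this outcome are worth keeping when they cost almost nothing.

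**Working it through.** **Inputs from the article**
- Three sites; 1:1 blocked allocation within site.
- LOS: N=2500; 35% of patients with 1 day less, so a mean difference of 0.35 × 1 = 0.35 day; two-sided α=.01; 80% power at N=2356 (Table 2, row for 2.5 days, 35%, 1.0 day).

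**Input not in the article (assumed)**
- R², the share of LOS variance that lies between sites. Range taken: 0 to 20%, with 5% and 10% as the main cases.

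**Step 1. Reproduce the plan's LOS figure.** The article prints no standard deviation (SD), so solve for it from N=2356 at face value:

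SD = 0.35 × √(2356/4) / (2.576 + 0.842) ≈ 2.49 days.

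The expected z statistic at N=2500 is 3.417 × √(2500/2356) = 3.520. Power is Φ(3.520 − 2.576) = 82.8%, which agrees with the stated figure of more than 80%.

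**Step 2. Effect of site.** With blocking by site, the true standard error is √(1−R²) times the one the pooled test uses. At two-sided .01:
- stratified power = Φ(3.520/√(1−R²) − 2.576)
- unstratified power = Φ(3.520/√(1−R²) − 2.576/√(1−R²))
- true type I error of the unstratified test = 2 × [1 − Φ(2.576/√(1−R²))]

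| R² (assumed) | Unstratified power | Stratified power | Gain (points) | True type I error, unstratified |
|---|---|---|---|---|
| 0 | 82.8% | 82.8% | 0 | .0100 |
| 2% | 83.0% | 83.7% | 0.7 | .0093 |
| 5% | 83.4% | 85.0% | 1.6 | .0082 |
| 10% | 84.0% | 87.2% | 3.2 | .0066 |
| 20% | 85.5% | 91.3% | 5.9 | .0040 |

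Example, R²=5%: √.95 = 0.9747; 3.520/0.9747 = 3.612; 2.576/0.9747 = 2.643. Stratified: Φ(1.036) = 85.0%. Unstratified: Φ(0.969) = 83.4%.

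**Step 3. Simulation check.** The unstratified and van Elteren tests were simulated with total SD about 2.49, N=2500 and two-sided .01.

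| R² | Adjacent site means apart by | Unstratified power | Stratified power | Simulated type I error, unstratified |
|---|---|---|---|---|
| 0 | 0 days | 80.9% | 80.9% | .011 |
| 2% | 0.43 | 81.0% | 81.4% | .010 |
| 5% | 0.68 | 79.8% | 81.8% | .008 |
| 10% | 0.96 | 80.6% | 83.8% | .008 |
| 20% | 1.36 | 82.3% | 89.8% | .004 |

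Power is slightly lower than in Step 2, but the differences between tests agree in direction and rough size: 2.0 and 3.2 points at 5% and 10%.

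**Step 4. Sensitivity to the baseline.** Step 2 takes Table 2 at its stated α. If its sample sizes rested on a weaker criterion, the starting power would be lower. With z sum 3.168 in place of 3.417 (two-sided .02), the expected z is 3.168 × √(2500/2356) = 3.263. Unstratified versus stratified power becomes 76.0% versus 78.0% (R²=5%) and 76.6% versus 80.6% (R²=10%), gains of 2.0 and about 4 points. This sets the upper end of the range quoted here; the point does not depend on it.

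**Step 5. Fallback at α=.05.** If acute hospital care is significant, LOS is tested at .05. With 1.960 in place of 2.576 in Step 2, unstratified versus stratified power is 94.5% versus 95.1% (R²=5%) and 95.0% versus 96.0% (R²=10%), gains of about 0.5 and 1.0 point.

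**Step 6. Acute hospital care.** The stated 88.7% (14% versus 9.8%, α=.04, N=2500) is reproduced at 88.2 to 88.9% by unstratified formulas. In simulation with assumed site control rates from 14/14/14% to 7/14/21%, site strata change power by 0 to 0.6 points. The information ratio is 1.0000 to 1.0001, so the hazard-ratio interval does not narrow.

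**The case against.** The strongest reply is that nothing here is invalid. The unstratified test does not inflate the type I error, it matches the test behind Table 2, and its loss depends on between-hospital variation that the article never reports. Eligibility is limited to elective surgery with an expected stay of at most 3 days, which may keep that variation small. If acute hospital care succeeds, LOS is tested at .05 and the gain shrinks to about a point or less. Recruitment and follow-up are complete, so changing a coprimary test now is more than a wording edit. All of this stands, and it is why the point is minor. It does not remove the mismatch between a stated design and a stated test.

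A reader might infer three stronger things, which the document does not support:
- **That the Cox model has no site strata.** A condensed article that points to a separate analysis plan is silent on this, and silence is not exclusion. The gain would in any case be negligible (Step 6).
- **That confidence intervals are too wide.** The article specifies no interval for LOS, and the hazard-ratio interval does not narrow with site strata.
- **That LOS power is already below 80%, so these points are decisive.** This requires reading Table 2 at an α other than the one stated. It is a separate question about that table and adds no weight here.

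**Conclusion.** The point holds for index LOS only, as a minor efficiency improvement. Site-stratified randomisation is paired with a named unstratified test. If hospitals differ in LOS, that test is conservative: true type I error is about .008 or .007 at nominal .01, with about 1.6 to 2 or 3 to 4 points of power lost, when site explains 5% or 10% of LOS variance. Those shares are assumptions; at 2% the loss is under one point, and at zero there is none. The direction is certain whenever sites differ, but the size is not known from the article. The trial's conclusions would remain valid under the test as written.

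**What to change.** Before investigators are unblinded, name a site-stratified (van Elteren) Wilcoxon test as the primary test for index LOS, at the same α (.01, or .05 under the fallback), and keep the unstratified test as a sensitivity analysis. When doing so, it would also help to state whether the Cox model for acute hospital care is stratified by site; this is for clarity, not power.

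The cost is small. With three strata and 2500 patients, sparse cells are unlikely, and stratifying loses essentially no power if the hospitals turn out alike. Because follow-up is complete and the article describes analysis as underway, the change should be a dated, justified amendment made blind to results. If unblinding has already taken place, the named test should stay primary and the stratified test be reported as supportive.

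### Secondary and tertiary outcomes are tested one way and estimated another, with neither named as decisive; in practice this matters mainly for one tertiary outcome, quality of life

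*Protocol article*

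**What the plan says.** The Statistical Analyses section of the protocol article gives two sets of methods for the same secondary and tertiary outcomes.

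- Tests: "we will use the chi-square test for binary or categorical variables and the 2-sample *t* test for continuous variables".
- Estimates for binary outcomes: "We will assess the effect of VC-RAM using log-binomial regression models and report the corresponding relative risks and 95% CIs".
- Estimates for continuous outcomes: "For continuous outcomes, we will evaluate the intervention effect using analysis of covariance regression models to obtain effect estimates and their 95% CIs".
- Threshold: "The α level for all secondary and tertiary outcomes will be set at .05".
- Interpretation: "we will not adjust for multiple testing as we will be evaluating the consistency of effect, number of outcomes, and size of the effect".

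No covariates are named for either model, and no sentence says whether the simple test or the model determines that an outcome is positive.

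Two other sections bear on this. Follow-Up states "The EQ-5D-5L is administered at baseline and day 30", while the pain questionnaire is given on days 15 and 30 only. Randomization describes "block randomization with varying block sizes stratified by site". Health-related quality of life appears in the tertiary list under Trial Outcomes.

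**The concern.** A 2-sample t test uses only the follow-up values. An analysis of covariance, by its nature, adjusts for at least one covariate. Where a baseline measurement exists and predicts the follow-up value, the two analyses use different standard errors and give somewhat different estimates. A published P value can then fall on one side of .05 while the 95% CI beside it says the opposite.

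The article intends to weigh non-primary results by how many are positive, how consistent they are and how large the effects are. With two analyses available and neither designated, the positive verdict and the effect size could come from different analyses, or the choice could be made after both are seen. If the t test is the one that counts, it also discards baseline information that the trial collects and that the planned model would presumably use.

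**Working it through.** **Inputs from the article.** 1250 patients per arm and 1:1 allocation (Sample Size Calculations, Randomization); alpha .05 for non-primary outcomes, taken as two-sided; EQ-5D-5L at baseline and day 30 (Follow-Up).

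**Assumptions, because the article gives no figure.** The correlation r between baseline and day-30 EQ-5D-5L; that ANCOVA adjusts for baseline; complete EQ-5D-5L data.

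**Check of the design inputs.** The article states no power for any secondary or tertiary outcome, so the only figure to reproduce is the one for acute hospital care: 88.7% for 14% versus 9.8% at two-sided alpha .04. The hazard ratio is ln(1 − 0.098)/ln(1 − 0.14) = 0.684, and expected events are 1250 × (0.14 + 0.098) = 297.5. The Schoenfeld formula gives Φ(√297.5/2 × |ln 0.684| − 2.054) = 88.9%, which agrees.

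**Power for quality of life.** Adjusting for baseline multiplies the outcome SD by √(1 − r²). If ANCOVA has 80% power, its expected z is 1.960 + 0.842 = 2.802. The expected z of the t test is 2.802 × √(1 − r²), so its power is Φ(2.802 × √(1 − r²) − 1.960):

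- r = 0.3: Φ(2.673 − 1.960) = 76%
- r = 0.5: Φ(2.426 − 1.960) = 68%
- r = 0.6: Φ(2.241 − 1.960) = 61%

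**Disagreement between the two verdicts.** In large samples z_t = √(1 − r²) × z_ANCOVA + r × z_baseline, where z_baseline is an independent standard normal. Simulating this pair at two-sided .05 gives:

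| r | t-test power (ANCOVA 80%) | Disagree, ANCOVA 80% | Disagree, no effect |
|---|---|---|---|
| 0 | 80% | 0% | 0% |
| 0.3 | 76% | 8% | 2.8% |
| 0.5 | 68% | 17% | 4.7% |
| 0.6 | 61% | 23% | 5.6% |

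Most disagreements under an effect run one way. At r = 0.5 the ANCOVA interval excludes zero while the t test is not significant in 14.4% of trials; the reverse happens in 2.3%. With no effect, each method alone holds about 5%. If either could be used to claim a result, the error rate is 5% plus half the disagreement: 6.4%, 7.3% and 7.8% for r = 0.3, 0.5 and 0.6.

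**The other scale.** Fix the t test at 80% power instead, which at 1250 per arm is a difference of 2.802 × √(2/1250) = 0.112 SD. ANCOVA then has 83.6%, 89.9% and 93.8% for r = 0.3, 0.5 and 0.6. To match it, the t test would need 1/(1 − r²) = 1.10, 1.33 and 1.56 times the sample.

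**Larger effects.** The expected z of the t test is d × √(1250/2) = 25d for a standardised difference d. At an assumed d of 0.15 (z = 3.75) the t test has 96% power and disagreement is about 2% to 3%. At d = 0.20 (z = 5.0) both exceed 99.8% and disagreement is about 0.1%.

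**Binary outcomes.** Comparing an uncorrected chi-square test with the Wald interval of an unadjusted log-binomial model, at 1250 per arm and 400,000 simulated trials per setting, disagreement ranged from 0.05% (14% versus 14%) to 1.7% (2% versus 1%). With a continuity correction it was 0.6% to 5.9%.

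**The case against.** The strongest reply is that this belongs to the statistical analysis plan, which the article says will be finalized before any investigator is unblinded. A simple test paired with a model-based estimate is a common layout, both methods are valid, and covariates are routinely left to that plan. That stands for the missing covariate list, which is not the point here. It does not dispose of the rest: the article itself names two procedures for the same outcomes, and an analysis plan that took the P value from ANCOVA would depart from the test published here.

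A reader might infer that power for quality of life is definitely lost. The documents do not support that. The article never says the t test alone decides, and its wording that ANCOVA evaluates the intervention effect can be read as making ANCOVA the effect analysis already, in which case nothing is lost. The loss also depends on a correlation the article does not give.

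A reader might also infer that the secondary outcomes are affected broadly. They are not. Quality of life is tertiary. Nearly all the listed secondary outcomes are binary or proportions, where an unadjusted log-binomial interval and an uncorrected chi-square test almost always agree. Pain has no stated baseline, and days in hospital has none to adjust for.

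Finally, the 8% to 23% disagreement applies to effects near the limit of detection. That is correct, and larger effects make the issue nearly disappear.

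**Conclusion.** The point holds in a limited form. The article states two procedures for secondary and tertiary outcomes and does not say which decides significance, and the named t test makes no use of the baseline EQ-5D-5L. Its practical weight falls mainly on one tertiary outcome.

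The size is conditional on three things: the t test supplying the P value, ANCOVA adjusting for baseline, and a correlation of 0.3 to 0.6. Under those conditions the t test gives up roughly 4 to 19 points against an ANCOVA with 80% power (80 − 76 and 80 − 61). At zero correlation it gives up nothing.

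Type I error is sound for either analysis used alone; it rises above 5% only if the choice is left open. The coprimary conclusions are unaffected. This is a worthwhile clarification with an efficiency gain, not a flaw that threatens the trial.

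**What to change.** Before unblinding, state that for quality of life the P value, estimate and 95% CI all come from one ANCOVA of day-30 EQ-5D-5L, adjusted for baseline EQ-5D-5L and site. For every other secondary and tertiary outcome, take the P value from the same model as the interval, including site as the stratification factor where the model converges.

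An adjusted log-binomial model may fail to converge, particularly for rare outcomes, so name the fallback in advance.

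The change needs no new data and reduces the number of analyses. Its costs are the wording and the convergence risk just described. Timing matters: recruitment ended in October 2024 and the abstract reports that analysis is underway. If unblinding has already occurred, report the tests named in the article alongside the model-based results, so that the change cannot be taken for a choice made after seeing the data.
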